# Does additional extracorporeal shock wave therapy improve the effect of isolated percutaneous radiofrequency coblation in patients with insertional Achilles tendinopathy? Study protocol for a randomized controlled clinical trial

**DOI:** 10.1186/s13063-022-06847-z

**Published:** 2022-11-07

**Keywords:** Achilles tendinopathy, Percutaneous radiofrequency coblation, Extracorporeal shockwave therapy, Randomized controlled trial, Protocol

## Abstract

**Background:**

No conclusive evidence recommends a prior treatment for insertional Achilles tendinopathy (IAT). It is theorized that both percutaneous radiofrequency coblation and extracorporeal shockwave therapy (ESWT) relieve pain within the insertion. However, no clinical evidence shows that either treatment promotes the regeneration of the tendon or if the combination of these 2 interventions offers better function and less pain than one therapy.

**Methods:**

The study is a randomized, controlled trial with patients allocated in a 1:1 ratio to one of two parallel groups. Patients with insertional Achilles tendinopathy who are not satisfied with the effect of conservative treatment will be screened. A minimum of 38 patients will be enrolled after deciding to participate in the trial on an informed basis. Then the intervention group and the control group perform radial ESWT and sham-ESWT respectively at 6 months after percutaneous radiofrequency coblation. The primary outcome will be the Victorian Institute of Sports Assessment Achilles (VISA-A) Score. Secondary outcome measures will be Foot and Ankle Outcome Score (FAOS) scale, visual analog scale (VAS), Tegner Score, and MRI ultra-short echo time (UTE) T2* value. The assessments will occur in 6 months, 1 year, and 2 years, post-operatively. The differences between the 2 groups will be conducted as intention-to-treat basis.

**Discussion:**

We aim to investigate if radiofrequency coblation associated with ESWT can provide more encouraging imaging findings as well as functional and clinical outcomes regarding the treatment of the IAT comparing to the single radiofrequency coblation treatment.

**Trial registration:**

ChiCTR1800017898; pre-results. Registered on 20 August 2018.

**Supplementary Information:**

The online version contains supplementary material available at 10.1186/s13063-022-06847-z.

## Background

Achilles tendinopathy is a common disorder in sports and daily life. This injury is frequently encountered in middle- and long-distance runners with up to 36% incidence rate [1–3] and may cause up to 5% of professional athletes to a premature career end [4, 5]. Achilles tendinopathy is considered as a multifactorial condition whose exact etiology remains to be determined and can be divided into insertional and non-insertional tendinopathy according to its anatomical location. Insertional Achilles tendinopathy (IAT) is responsible for roughly 20–24% of all Achilles disorders [6]. Patients with IAT complain about compromised function and gradual onset of pain at the calcaneal attachment of the Achilles tendon and could be aggravated by standing, walking, and jogging.

The initial treatment is conservative management, such as eccentric exercises [7, 8], anti-inflammatory drugs (NSAIDs) [9], extracorporeal shockwave therapy [10–12], and platelet-rich plasma (PRP) therapy [13, 14]. If nonoperative treatment fails, surgery might be taken into consideration. Most surgical procedures involve debridement and decompression of Achilles tendon insertion and augmentation in case of excessive tendon loss [15]. To date, there is no gold standard treatment for IAT. Scientific evidence shows variable and inconsistent effects among different treatments [16, 17], meaning to provide a most effective management with high-quality and reliable evidence is urgently needed.

It is reported that 25 to 50% of patients with chronic tendinopathy may undergo surgery [18–20]. Percutaneous radiofrequency coblation as a minimally invasive treatment has been used in the management of lateral epicondylitis [21, 22], rotator cuff tendinopathy [23], and foot and ankle tendinosis [24]. It would reduce surgical time and facilitate an earlier return to activity. The procedure has been shown to induce degeneration of sensory nerve fibers and improves vascularity [25, 26], which, in its turn, relieves the pain and regenerates the tendon tissue, respectively. Extracorporeal shockwave therapy which is widely used in Achilles tendinopathy also shares a similar mechanism theoretically [25]. However, no clinical evidence shows those two treatments promote the regeneration and quality of the tendon.

Grosse et al. [27], Gardin et al. [28], and Juras et al. [29] reported that there was statistical significance in UTE-T2* value between magnetic resonance imaging (MRI) images of patients with IAT and normal population, which indicates that MRI UTE-T2* can be applied in clinical quantitative assessment to monitor the morphological information of the tendon and produce reliable results. In addition, the correlation between MRI UTE-T2* and clinical score can be determined.

Our aim is to evaluate the effectiveness of percutaneous radiofrequency coblation associated with an ESWT protocol and compare it to isolated radiofrequency coblation, via VISA-A score [30] primarily and MRI UTE-T2* secondarily. It is hypothesized that adjunctive ESWT will promote tendon regeneration, mitigate pain, and improve function as compared to a controlled group.

## Methods/design

The protocol will be reported in accordance with the guidelines and checklists for Standard Protocol Items: Recommendations for Interventional Trials (SPIRIT).

### Aim, design, and setting

We aim to investigate if radiofrequency coblation associated with ESWT can provide more encouraging outcomes regarding the treatment of the IAT with trustworthy evidence.

This study is a randomized, double-blinded, parallel-group clinical trial (Fig. 1). The 1:1 allocation to either receive radial ESWT or sham-ESWT, after surgery is conducted using computer-generated random allocation sequences and sealed envelopes. The patients of the placebo group will also experience ESWT’s procedure, while the apparatus’ therapeutic head will be placed a support, which will block the propagation of shock waves without changing the equipment’s appearance, noise, and using process. Furthermore, the patients will feel the vibration of the machine, but the insertional region won’t be directly stimulated. The physiotherapists will not take any part in the posttreatment assessment of the patients. The outcome data will be collected by research fellows who are blinded to the treatment procedures to reduce the risk of assessment bias. The SPIRIT Figure shows in detail the schedule of enrollment and assessments (Fig. 2).

**Fig. 1 Fig1:**
[figure not shown]
Participant flow diagram

**Fig. 2 Fig2:**
[figure not shown]
Standard Protocol Items: Recommendations for Interventional Trials (SPIRIT) Figure

### Characteristics of participants

Patients referred to the Department of Sports Medicine, Huashan Hospital, Fudan University with insertional Achilles tendinopathy who had no symptom relief after 3 to 6 months of conservative therapy [31] other than ESWT are assessed for eligibility. The diagnosis is based on a medical history and clinical examination including persistent pain at the calcaneus tendon insertion region, and ultrasound or MRI results confirm it.

### Inclusion criteria

The inclusion criteria are as follows:Medical history, clinical examination, and ultrasound or MRI results conform to the diagnosis of IAT.Age 18–65 years, both genders.The patient has decided to accept percutaneous radiofrequency coblation and radial ESWT.The patient must be expected to be able to attend post-operation examinations.The patient must be able to give informed consent.

### Exclusion criteria

The exclusion criteria are as follows:Previous surgery on the affected limb.The patient would not be able to strictly follow trial procedures or complete questionnaires.Non-insertional or mixed tendinopathy (insertional and non-insertional).Pregnancy or intention to be pregnant.Currently undergoing follow-up and treatment in a psychiatry department or by other mental health professionals.

### Withdrawals

Participants may decline to continue from the trial at any time without prejudice and still encouraged to keep in touch and welcomed to inquiry and ask for necessary help.

Other reasons for discontinuation include:The patient develops Achilles tendon rupture.The patient develops complex or increasing regional pain.Other unexpected and unpredictable circumstances when the research team judges that the risk of continuing the protocol treatment is greater than the benefit.

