### Sample size

The primary outcome of this study is the VISA-A score. McCormack J et al. [32] have identified the minimum clinically important difference (MCID) of 6.5 points for the VISA-A. The study of Wei M et al. [33] indicates an expected standard deviation (SD) of 6.9 points. We have referred to the sample size calculation method of Kvalvaag E et al. [34]. To detect a difference in results between the radical ESWT and the sham-ESWT participants at a level of 5% significance and the most likely scenario for 80% power, 15 patients per group will be needed. Assuming a margin of 20% loss of primary outcome data, we propose to recruit a minimum of 38 patients in total.

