### Primary outcome

#### Victorian Institute of Sports Assessment Achilles (VISA-A) score

The VISA-A score is a validated questionnaire for Achilles tendinopathy and contains 8 questions assessing physical activity and pain (0, no activity/maximum pain; 100, maximum activity/no pain) [34]. And it is adapted to the local language. The Chinese version has been used in clinical trials [37, 38], proving its validity (Additional file 1).

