### Statistical analysis

All continuous data from primary and secondary outcome measurements will be summarized by descriptive statistics with the number of observations (*n*), mean, SD, minimum, median and maximum. Uncontinuous data such as co-morbidities concomitant injuries will be summarized by descriptive statistics with the number of observations, calculating the incidence separately and analyzing whether it is associated with prognosis. The primary point for analyses of efficacy will be 6 months after surgery, then 1 year and 2 years. A statistical software program (SPSS for Windows, version 23.0; SPSS Inc, Chicago, IL) will be used for statistical analysis in this study. Group comparison will be statistically analyzed by either Student’s *t* test or Mann-Whitney *U* test, depending on whether the data is normally distributed. The significance level will be set at a *p* value <0.05.

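### The Withdrawals section does not separate stopping ESWT or sham from ending follow-up, so patients with rupture or increasing pain could be lost selectively from a pain-and-function endpoint

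*Protocol article*

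**What the plan says.** The Withdrawals section of the protocol article opens with voluntary departure: "Participants may decline to continue from the trial at any time without prejudice and still encouraged to keep in touch". It then gives further grounds for discontinuation. The first two are "The patient develops Achilles tendon rupture" and "The patient develops complex or increasing regional pain". The last is the research team's judgement that "the risk of continuing the protocol treatment is greater than the benefit". The section does not state whether outcome assessments continue once one of these grounds is met.

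The primary outcome, VISA-A, "contains 8 questions assessing physical activity and pain" and runs from 0 to 100, with higher scores better. The abstract promises that "The differences between the 2 groups will be conducted as intention-to-treat basis". Under Statistical analysis the protocol states that "Group comparison will be statistically analyzed by either Student’s" t test or the Mann-Whitney U test, according to normality. The Sample size section recruits 38 patients, "Assuming a margin of 20% loss of primary outcome data".

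According to Procedures, patients are randomised after surgery and the four weekly ESWT or sham sessions start at 6 months. Outcomes are assessed at enrolment and at 6 months, 1 year and 2 years after surgery.

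**The concern.** Rupture and increasing pain are not incidental reasons for leaving. They are what a low VISA-A score records. The section places them under a heading about withdrawal, next to patients who leave the trial, so site staff could reasonably stop all visits once such an event occurs. Patients would then be missing because they did badly, and the remaining comparison would no longer cover everyone randomised.

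At stake are the 1- and 2-year comparisons, the only scheduled ones that follow ESWT. If more sham patients worsen and leave, a real benefit is understated. If ESWT itself provokes pain or rupture, the ESWT arm loses its worst patients and harm is masked. The protocol's section on adverse events counts rupture among the presumed complications of ESWT as well as of coblation. Who stays in follow-up is decided during conduct, and no later analysis plan can recover a score that was never collected.

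**Working it through.** **Passages side by side**

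- *For leaving the trial:* the heading, the opening sentence on patients who leave, and the way the list continues from that sentence.
- *For stopping treatment only:* the last item, which weighs the risk of continuing protocol treatment.
- *Silent:* whether VISA-A is still collected afterwards. Encouraging patients to stay in contact is not a rule on outcome collection.

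The first reading is hard to square with the intention-to-treat statement in the abstract. The second is compatible with it. The text does not choose.

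**The plan's own figure for loss**

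The stated need is 15 per group, 30 in total. With 20% loss, 30 / (1 − 0.20) = 37.5, rounded up to 38, which reproduces the plan's total. This is a general allowance and is not tied to rupture or pain.

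**Illustration of size**

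Inputs from the Sample size section: SD 6.9 and MCID 6.5. Assumptions: VISA-A is normally distributed, and those lost are exactly the lowest scorers. The documents give no rate for either event, so a range is shown.

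If the lowest fraction q of one arm is lost, the mean of those who remain rises by

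shift = SD × φ(z_q) / (1 − q),

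where z_q is the q-quantile of the standard normal distribution and φ its density.

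| Lost in one arm only | Calculation | Shift (points) | Share of 6.5 |
|---|---|---|---|
| 5% | 6.9 × 0.103 / 0.95 | 0.75 | 12% |
| 10% | 6.9 × 0.1755 / 0.90 | 1.35 | 21% |
| 20% | 6.9 × 0.280 / 0.80 | 2.41 | 37% |

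With no true effect and equal loss in both arms, the two shifts cancel and the bias is 0.

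If the true difference is 6.5 in favour of ESWT and everyone below a common score is lost, the sham arm loses more:

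| Sham lost | ESWT lost | Expected difference among those left |
|---|---|---|
| 5% | 0.5% | 5.85 |
| 10% | 1.3% | 5.39 |
| 20% | 3.7% | 4.67 |

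For the 10% row: the sham mean rises by 1.35 and the ESWT mean by about 0.24, so 6.5 + 0.24 − 1.35 = 5.39.

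**Timing**

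An event before 6 months cannot be caused by ESWT or sham, because neither has been given. Treatment-driven differential loss can therefore affect only the 1- and 2-year assessments.

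**The case against.** The strongest defence is that the section can be read as stopping protocol treatment only. Its last item says so in terms, nothing states that outcome collection ends, and complications and adverse events are recorded in any case, so a rupture would not vanish from the report. On that reading there is no conflict with intention-to-treat. This stands as far as it goes: the text is ambiguous and does not contradict itself outright. It does not remove the point, because staff following the heading and opening sentence could stop VISA-A collection, and a recorded complication does not replace a missing score.

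A reader might go further and infer that the plan compares completers, or that data are missing not at random by design. The documents do not say this. Naming a t test or Mann-Whitney U test fixes neither the analysis set nor the treatment of missing scores; both are commonly left to a full protocol or SAP that is not shown, and their absence is no finding. Nor can the 20% allowance be taken as the expected number of pain or rupture withdrawals; it is ordinary attrition planning.

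A reader might also expect a large rise in false positives. In simulation with 19 per arm, SD 6.9 and no true effect, losing the worst 3 in one arm and the worst 1 in the other gives about 11% rejection. Losing the worst 2 in each arm, with no bias at all, already gives about 8%. About half of the rise above 5% therefore comes from trimming the extreme ranks, which shrinks the observed SD. That figure should not be read as a measure of the bias.

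**Conclusion.** The point holds as a defect of wording with consequences for the data. The Withdrawals section must be reconciled with the intention-to-treat statement, because one natural reading of it removes patients on account of a poor value of the primary endpoint.

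The size cannot be derived from the documents. The figures of 1.35 and 2.41 points for 10% and 20% loss rest on normal scores, SD 6.9, loss of exactly the lowest scorers and loss in one arm only. Weaker selection or more balanced loss gives a smaller bias. The direction is not fixed. Whether rupture or pain should lead to stopping the study sessions is a clinical rule and is not assessed here.

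**What to change.** In the Withdrawals section, state three things:

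1. Meeting a discontinuation criterion ends only the study ESWT or sham sessions.
2. VISA-A and the other outcomes are still collected at the remaining scheduled visits, unless the patient withdraws consent to follow-up.
3. All randomised patients are analysed in their assigned arm, with adjustment for VISA-A already collected before ESWT. The enrolment score always qualifies; the 6-month score does if it is taken before the first session.

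A sensitivity analysis for patients whose scores are still missing after rupture or worsening pain is optional and may be left to the SAP. The discontinuation criteria stay as they are.

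The cost is a few sentences, a covariate in the analysis and continued use of visits and questionnaires that are already scheduled.

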### Sample size

The primary outcome of this study is the VISA-A score. McCormack J et al. [32] have identified the minimum clinically important difference (MCID) of 6.5 points for the VISA-A. The study of Wei M et al. [33] indicates an expected standard deviation (SD) of 6.9 points. We have referred to the sample size calculation method of Kvalvaag E et al. [34]. To detect a difference in results between the radical ESWT and the sham-ESWT participants at a level of 5% significance and the most likely scenario for 80% power, 15 patients per group will be needed. Assuming a margin of 20% loss of primary outcome data, we propose to recruit a minimum of 38 patients in total.

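### Sidedness is not stated: 15 per group matches only a one-sided 5% t test; read two-sided, power is about 70% after the planned loss

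*Protocol article*

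**What the plan says.** All the inputs are in the Sample size section of the protocol article. A cited study is said to "have identified the minimum clinically important difference (MCID) of 6.5 points for the VISA-A", and a second cited study "indicates an expected standard deviation (SD) of 6.9 points". The calculation method is taken from a third cited trial and is not described. The result is that "at a level of 5% significance and the most likely scenario for 80% power, 15 patients per group will be needed". The recruitment figure follows: "Assuming a margin of 20% loss of primary outcome data, we propose to recruit a minimum of 38 patients in total".

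The Abstract gives the allocation: "patients allocated in a 1:1 ratio to one of two parallel groups". The Statistical analysis section plans a Student's t test or a Mann-Whitney U test, chosen on normality, with significance declared at p<0.05. Neither section says whether the test is one-sided or two-sided. The only directional wording is the research hypothesis in the Background: "It is hypothesized that adjunctive ESWT will promote tendon regeneration, mitigate pain, and improve function as compared to a controlled group".

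**The concern.** A 5% level with no direction attached is normally read as two-sided. On that reading, 15 per group falls short of 80% power for the stated difference and SD. The recruitment target of 38 is built on 15 per group, so any shortfall carries through to the patients expected to remain after loss.

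At stake is how a null result will be read. A reader who trusts the stated 80% would take the chance of missing a true 6.5-point effect to be 20%. If the test is run two-sided and the planned loss occurs, that chance is about 30%. If a one-sided 5% test was intended, readers need to know for a different reason: a false claim of benefit then has a 5% chance, not the 2.5% that a two-sided 5% test allows in that direction.

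**Working it through.** **Inputs** (Sample size section unless noted)
- Difference δ = 6.5 points; SD σ = 6.9 points; standardised difference d = 6.5/6.9 = 0.942.
- Significance level 5%, sidedness not stated; power 80%.
- Allocation 1:1 (Abstract); unadjusted two-group comparison (Statistical analysis).
- Loss of primary outcome data 20%.

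**Formulas**
- Normal approximation: n per group = 2(z_α + z_β)²(σ/δ)².
- t test: smallest n at which a noncentral t variable with 2n − 2 degrees of freedom and noncentrality d√(n/2) exceeds the critical value with probability at least 0.80.

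**Step 1: reproduce the stated 15 (one-sided 5%)**
- Normal: 2 × (1.645 + 0.842)² × (6.9/6.5)² = 13.93, so 14.
- t test: n = 14.66, so **15**. Power at 15 per group is 80.8%; at 14 it is 78.3%.

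The stated figure is matched exactly by the one-sided t test.

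**Step 2: reproduce the stated 38**
- 2 × 15 = 30 evaluable; 30/(1 − 0.20) = 37.5, so **38**.

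The loss allowance is applied correctly. In reverse, 38 × 0.8 = 30.4, or about 15 evaluable per group, which is the number the plan itself expects to analyse.

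**Step 3: the same inputs, two-sided 5%**
- Normal: 2 × (1.960 + 0.842)² × (6.9/6.5)² = 17.69, so 18.
- t test: n = 18.70, so **19**.

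Neither gives 15.

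**Step 4: power for 6.5 points, t test**

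| Evaluable per group | One-sided 5% | Two-sided 5% |
|---|---|---|
| 15 (after 20% loss) | 80.8% | 70.2% |
| 18 | 87.0% | 78.4% |
| 19 (no loss) | 88.6% | 80.7% |

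By the normal approximation, two-sided power at 15 per group is 73.2%, so the choice of formula does not close the gap.

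**Step 5: what 15 per group can detect two-sided with 80% power**
- With SD 6.9, a difference of 7.31 points, which is 0.81 above the stated MCID of 6.5.
- Equivalently, 6.5 points would be detectable only if the SD were about 6.13.

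**Step 6: recruitment that would hold 80% two-sided after 20% loss**
- 19/0.8 = 23.75, so 24 per group, 48 in total.

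**The case against.** The strongest reply is that nothing has been miscalculated. The article never says two-sided, the hypothesis in the Background is directional, and the inputs reproduce 15 and then 38 exactly under a one-sided 5% t test. This stands. A reader might infer that 15 is an arithmetic error, or that the design cannot have 80% power at 5%; the document supports neither. It does not settle the matter, because a directional research hypothesis is not a declaration of a one-sided test, the sample size target is worded without direction, and an unqualified p<0.05 is ordinarily two-sided.

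A second reply is that the method comes from a cited trial that is not shown, that "the most likely scenario for 80% power" hints at other scenarios, and that a journal article condenses a fuller plan. This limits certainty about what was intended. It does not remove the point, which is not mere silence: the level, power, difference, SD and sample size are all printed, and they fit together only under the less usual reading.

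A third reply is that 70% is the worst planned case. This is fair. With less than 20% loss, two-sided power lies between 70.2% and 80.7%, and 38 is described as a minimum. Against that, the Procedures section numbers the randomisation envelopes 1 to 38, so more recruits do not appear to be expected.

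A reader might also go further in either direction: that true power is lower still because the SD could exceed 6.9 or the Mann-Whitney test could be used, or that a baseline-adjusted analysis would rescue 15 per group. The document gives no other SD, no non-normal scenario to calculate from and no baseline correlation, and it describes an unadjusted comparison. None of these belongs in the finding.

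**Conclusion.** The point holds as an undeclared assumption with a material consequence. The 15 per group depends on a one-sided 5% t test that the article does not declare. On the conventional two-sided reading, the stated 80% power for 6.5 points becomes about 70% at the sample size expected after loss, and the type II error about 30%. The 80% is then met only if none of the 38 is lost.

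These figures assume a difference of 6.5, an SD of 6.9, equal groups, an unadjusted t test and the full 20% loss. The arithmetic is certain under those assumptions. What remains uncertain is which sidedness the authors intended, and only they can say. Under either answer the text needs correcting: if two-sided, the power is overstated; if one-sided, an essential design feature is missing.

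**What to change.** State the sidedness of the primary test in both Sample size and Statistical analysis.

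- **If two-sided**, replace the power statement with wording such as: *38 recruited, about 15 per group evaluable after 20% loss, gives about 70% power (two-sided 5%, unadjusted t test) for 6.5 points with SD 6.9; about 81% if there is no loss.*
- **If one-sided 5% was intended**, declare and justify it in both sections, and report the two-sided power alongside.

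The cost is wording only. In the two-sided case the stated power becomes less favourable. No extra patients are required; the total of 48 in Step 6 shows the size of the gap and is not a demand to enlarge the trial.
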